#### Integrative analysis

Consistent with our earlier work [24], we will seek to integrate findings between:i)Data sources within the process evaluation through common data management and coding.ii)Process evaluation objectives. For example, what the approach to tailoring tells us about fidelity of enactment and engagement with the intervention.iii)Component studies, through integrative workshops to understand what the findings from each mean to the others and to identify avenues for exploration. For example, if our trial identifies differential effect based upon deprivation, the process evaluation could explore the inclusion of deprivation in identification of actions by PCNs.

Integration will happen through team meetings and integrative workshops involving project team and wider stakeholders, as appropriate.

### Economic evaluation

An analysis plan will be written following Bristol Health Economics Analysis Plan (HEAP) guidance [25] and, as far as possible, the evaluation will align with the trial statistical analysis plan and adhere to the NICE reference case. All analyses will adopt the NHSE perspective and all cost and QALY measures will be discounted at the rate of 3.5% per annum. Our analysis will comprise three components:Within-trial economic evaluation and budget impact analyses.Design: An intention-to-treat, cost-effectiveness and cost-consequence analysis with a time horizon of 18 months and budget impact analysis using patient-level NDA data and intervention cost data.Data collection: Within-trial biomarker and resource use data collected through the NDA between baseline and 18 months post-randomisation will be used to assess health outcomes and healthcare costs. Healthcare cost data will include primary care prescriptions (glucose lowering drugs, antihypertensives and statins), inpatient (diagnosis, procedure, length of stay) and some outpatient data. The incremental costs of the two interventions when compared to NDA feedback alone will be assessed using a bottom-up, micro-costing approach [26]. This will draw on resource use data collected from people involved in facilitation delivery (e.g. NDA improvement lead, NDA administrator) as a fully integrated component within the interviews and surveys conducted as part of the process evaluation. These resources are likely to span intervention refinement, delivery and response activities; consumable costs incurred (e.g. printed material) and staff time (and grade) required; and additional activities that result from the intervention (e.g. meetings with stakeholders, local team training, additional consultations with patients).Analysis: The within-trial cost-effectiveness analysis will assess cost per unit change in HbA1c. The cost-consequence analysis will assess changes in all other NDA biomarker outcomes (e.g. cholesterol). Each resource use item, including staff time, will be costed using unit cost data available from routine sources, e.g. national healthcare databases such as Personal Social Services Research Unit (PSSRU) data [27, 28]. We will seek to capture the variance in costs that might occur across centres and incorporate this uncertainty in the analysis. We will also empirically estimate the denominator sample for deriving the per patient intervention cost. Given the high incidence and prevalence of type 2 diabetes in young adults, and thus potentially large ongoing costs to NHSE of delivering the intervention, an NHSE-wide budget impact assessment will also be conducted. Cost and outcome data will also be analysed for equity relevant subgroups as defined in the trial statistical analysis to inform the equity informative cost-effectiveness analysis (see below).Lifetime cost-utility analysis:Design: An intention-to-treat, cost-utility analysis with a time horizon of a lifetime, using intervention cost data, patient-level NDA data and the UK Prospective Diabetes Study Outcomes Model 2 (UKPDS-OM2) patient-level simulation model [29].Analysis: The patient-level demographic (e.g. age, ethnicity) and biomarker data collected during the within-trial period will be used as inputs to the UKPDS Outcomes Model v2.2 [29], which is a commercially available microsimulation model, pre-built, externally and internally validated, and recently updated by the University of Oxford to project long-term type 2 diabetes outcomes. The model will be used to estimate incremental lifetime healthcare costs and QALYs between the waitlist control and intervention groups by forecasting annually until death the progression of cardiovascular and type 2 diabetes complication risk factors (e.g. cholesterol, HbA1c, heart rate, smoking status, systolic blood pressure, weight, time since diabetes diagnosis) and the occurrence of eight events (e.g. myocardial infarction, ischaemic heart disease, stroke, amputation, blindness, renal failure). The primary outcome measure will be an incremental cost effectiveness ratio (ICER) assessing the aggregate-level incremental cost per QALY. We will also report net (monetary) benefit, which is a rearrangement of the ICER and estimated as: (λ x QALYs) – Costs, where λ is the willingness to pay threshold per health gain (in the case of NICE,
£20,000-£30,000 per QALY). Sensitivity analysis will explore assumptions made in the analysis and parameter uncertainty (e.g., around treatment costs). Decision uncertainty will be illustrated using a scatter plot of incremental cost–QALY pairs (UKPDS-OM2 outputs with 1,000 inner loops and 5,000 bootstraps) and the cost-effectiveness acceptability curve (CEAC).Equity informative cost-utility analysisDesign: A distributional cost-utility analysis will be undertaken to evaluate the equity impact of the interventions on outcomes alongside average cost-effectiveness [30, 31].Data collection: Audit data collected throughout intervention delivery will be used to estimate model parameters to be used within the UKPDS-OM2 for equity groups of interest including socio-economic status, gender, and ethnicity. Data collected within the study will be disaggregated by these equity groups and analysed to inform model input data for each group. The UKPDS-OM2 will be used to estimate lifetime costs and outcomes for each equity group which will be combined to create a distribution of costs and outcomes across the population for analysis.Analysis: The distribution of costs and outcomes will be analysed according to equity-informative cost-effectiveness analysis principles [32]. The distribution of costs and outcomes in the control group (without the interventions) will be compared with the distribution of costs and outcomes with each intervention. The inequality in each distribution will be calculated (e.g., using absolute and relative measures of inequality) and compared to quantify the impact of each intervention on health inequalities. The overall equity impact will be plotted against the overall cost-effectiveness (results from the lifetime cost-effectiveness analysis) on the health-equity impact plane and any trade-offs between equity impacts and cost-effectiveness will be analysed. Disaggregated estimates of costs and outcomes for different groups will also be presented to demonstrate the extent to which different groups are expected to benefit from the interventions.

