The low- and medium-intensity feedback facilitation interventions include overlapping behaviour change techniques but differ in terms of resource implications for both healthcare deliverers and PCN recipients. Where content is only delivered in the medium-intensity feedback facilitation (e.g. group delivery of content), this is depicted in the logic model (Appendix B).

PCNs will be offered the interventions to which they have been allocated via an email distributed from Diabetes UK via NHSE regions and ICBs. Staff in PCNs allocated to the medium intensity intervention will be invited to participate in 7 virtual workshops. Staff in PCNs allocated to the low intensity intervention will be offered access to asynchronous web-based training with email support. For each intervention arm, the emails inviting participation will be signed by the clinical and improvement lead and detail that the support for improvement is free, delivered by DiabetesUK and provides learning from higher performing PCNs, learning from young adults, help to identify high-risk population and best practice guidance. The invite will also describe the reason for focussing on young adults with type 2 diabetes and how the learning may help different goals, including improved outcomes, increased efficiency of care, evidence of quality improvement activity and may increase practice income. It will detail the target audience and invite them to register via a virtual registration form.

Waitlist control will receive usual NDA feedback alone. After the trial follow-up period, the PCNs allocated to this group will also receive feedback facilitation. The design will be informed by early process evaluation findings; the NDA contract requires delivery before trial data analysis is possible.

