### Outcomes

HbA1c level drawn from routine NDA data at 16-months post-randomisation in young adults with type 2 diabetes and baseline HbA1c ≥ 58 mmol/mol. We have chosen a 16-month follow-up period as it allows for a latent period for (i) PCNs and their member general practices to engage with facilitation, plan and initiate changes in clinical practice and (ii) for patients to consult, consider and start any new treatments or make any suggested lifestyle changes and for any benefits to be reflected in subsequent HbA1c measurements.

Secondary outcomes will comprise:Proportion with an HbA1c of < 58 mmol/mol.Proportion with an HbA1c of < 48 mmol/mol.Proportion prescribed both metformin and SGLT2 inhibitor.Proportion in whom the last blood pressure reading (measured in the preceding 12 months) is 140/80 mmHg or less (or equivalent home blood pressure reading).Proportion with statins prescribed.Proportion receiving NICE-recommended care processes in the preceding 12 months: blood pressure check; serum creatinine testing; urinary albumin: creatinine ratio testing; foot examination and risk classification; smoking status; retinal screening; body mass index; and referral to a structured education programme.

In young adults with baseline HbA1c ≥ 48 and < 58 measurement, we will examine the proportion with HbA1c ≥ 58 mmol/mol at follow-up to check for any unintended distributional consequences from focusing resources on those patients with higher HbA1c at baseline.

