### Data collection

Trial outcomes will be assessed using routinely collected individual patient data which is extracted from GP clinical systems by the NDA via the General Practice Extraction Service. We will use NDA-held demographic data in assessing effects on equity. The NDA validates, monitors and reports on data quality [4]; the NDA data quality report provides support that our selected measures are reliable.

The analysis will include outcome data from 12 months before randomisation to 16 months after randomisation.

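### The within-trial economic window runs to 18 months, two months past the 16-month follow-up after which waitlist PCNs may receive facilitation

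*Protocol article*

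**What the plan says.** The Economic evaluation section describes the first economic component as an intention-to-treat "cost-effectiveness and cost-consequence analysis with a time horizon of 18 months", together with a budget impact analysis. It repeats the 18 months for the data themselves: "Within-trial biomarker and resource use data collected through the NDA between baseline and 18 months post-randomisation will be used to assess health outcomes and healthcare" […]. The comparator for incremental intervention cost is NDA feedback alone, and the equity analysis describes the control group as being without the interventions.

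The other trial windows are 16 months. Under Outcomes, the primary outcome is "HbA1c level drawn from routine NDA data at 16-months post-randomisation", and the authors explain the length: "We have chosen a 16-month follow-up period as it allows for a latent period" for practices to act and for patients to respond. The Data collection section for the trial says: "The analysis will include outcome data from 12 months before randomisation to 16 months after randomisation". Appendix A (item 8) gives sites in both intervention arms 16 months of access.

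On the waitlist arm, the Intervention section says: "After the trial follow-up period, the PCNs allocated to this group will also receive feedback facilitation". It adds that the NDA contract requires this delivery before the trial data can be analysed. It gives no start month.

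**The concern.** The economic data are labelled within-trial but extend past the trial's own follow-up. The end of follow-up is also the point from which the control arm may be given facilitation. From month 16 the protocol no longer guarantees that control PCNs receive NDA feedback alone, which is the comparator the economic analysis names.

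What is at stake is the economic estimate. The article says it is unknown whether the medium-intensity intervention is cost-effective or whether that intensity is needed, so this analysis bears on a real commissioning decision. The 18-month data would supply the cost per unit change in HbA1c, the cost-consequence results and the budget impact. Within-trial biomarkers are also inputs to the lifetime model, and study data inform the equity model.

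**Working it through.** The plan has no calculated figure to reproduce on this point, and the sample size and power are not involved. The check sets the stated windows side by side.

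| Item | Where | Window |
|---|---|---|
| Economic time horizon | Economic evaluation | 18 months |
| NDA biomarker and resource-use data for the economics | Economic evaluation | baseline to month 18 |
| Follow-up period and primary outcome | Outcomes | 16 months |
| Trial outcome data | Data collection | month −12 to month +16 |
| Site access to the interventions | Appendix A, item 8 | 16 months |
| Facilitation for waitlist PCNs | Intervention | after follow-up; start month not given |

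**Excess window.** 18 − 16 = 2 months, and 2/18 = 11.1% of the economic horizon.

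**Exposure by waitlist start month.** The start month *s* is an assumption, because the article does not give it. The exposed share is (18 − *s*)/18 for *s* from 16 to 18, and zero after that:
- *s* = 16: 2/18 = 11.1%
- *s* = 17: 1/18 = 5.6%
- *s* = 18 or later: 0

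These are shares of calendar time in which the control arm could differ from its label. They are not estimates of bias.

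**Control PCNs concerned.** With 1283 PCNs allocated 1:1:1, 1283/3 = 427.7, so about 428 could be offered facilitation. This is an upper limit on exposure, because take-up is voluntary (Recruitment).

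**Which quantities are exposed if *s* is below 18.**
- *NDA-recorded healthcare costs* (prescriptions, inpatient and some outpatient care) accumulate to month 18 in every arm, so they are exposed.
- *Biomarkers* up to month 18 are exposed, but the article's own case for 16 months is that practices need time to change and patients need time to respond. At most two months of new facilitation would probably move control-arm HbA1c little.
- *Intervention costs* are built up by micro-costing for the two interventions, so the 18-month NDA window does not by itself alter them.
- *The primary effectiveness analysis* stops at month 16 and is not exposed.

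**Timing.** PCNs were allocated in April 2025 (Study progress). Month 16 is therefore about August 2026 and month 18 about October 2026, both after the article's publication in January 2026.

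**The case against.** The strongest reply is that contamination is possible but not established. The Intervention section says only that waitlist delivery follows follow-up. The contract clause sets a latest point for delivery and does not place its start at month 16. This stands: a reader might infer that months 16 to 18 are certainly contaminated, and the article does not say so.

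Three other strong inferences also fail.
- *Facilitation cost would be charged to the control arm and so lower the incremental cost.* The article costs the two interventions bottom-up, from those delivering facilitation and from process-evaluation interviews and surveys. Nothing says later waitlist facilitation is costed into the comparator.
- *Month-18 costs would be divided by a month-16 effect.* The Economic evaluation section runs both biomarkers and resource use to month 18, so this mismatch is not stated. What follows from the text is that the economic effect may be taken at a different time point from the trial's primary effect.
- *The 18-month window breaks a promise to align with the statistical analysis plan.* Alignment is promised only as far as possible.

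It can also be said that the 16-month data sentence concerns trial outcomes and does not expressly govern the economic data, and that a health economics analysis plan is still to be written. Both are true, but they do not remove the problem. The article itself fixes 18 months in print and ties release of the control arm to the end of a follow-up period it defines as 16 months. It neither explains the difference nor says how the two extra months are handled.

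**Conclusion.** The inconsistency is real and should be fixed. The economic window exceeds the trial's stated follow-up by two months, and after month 16 nothing in the article keeps the control arm on NDA feedback alone. The exposure is 0 to 2 of 18 months (at most 11.1%), depending on an unstated start month. If waitlist delivery starts before month 18, the randomised comparison of NDA-recorded healthcare costs is compromised for that part of the horizon, and the biomarker inputs to the lifetime and equity models probably only slightly. The documents do not allow the size or direction of the resulting bias in the cost-effectiveness ratio to be worked out. Whatever the start month, the economic evaluation and the primary analysis use different time points without explanation. The conclusion rests on reading the trial follow-up period in the waitlist sentence as the 16 months given under Outcomes, the only follow-up length the article defines.

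**What to change.** Reconcile the Economic evaluation section with the Intervention, Outcomes and Data collection sections, and carry the result into the health economics analysis plan before the data are extracted.

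The preferred change is to end the cost and biomarker window of the base-case within-trial analyses (cost-effectiveness, cost-consequence and budget impact) at 16 months post-randomisation, and to obtain later outcomes from the model. This keeps the comparator as named and puts the economic effect at the same time point as the primary effect. The cost is a change of wording and two months of resource-use data.

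If 18 months is intended, either of these would also resolve it:
- State that waitlist delivery begins only after month 18. This has to be checked against the NDA contract's timing requirement.
- Keep 18 months as a sensitivity analysis only, and say explicitly how months 16 to 18 are handled in the control arm.

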### Public involvement

In addition to involvement in intervention development described above, we are grateful for the involvement of young adults with diabetes in both our research team and intervention delivery team. As members of the team, they will review study progress and input into decisions about changes to protocol. Within the process evaluation, they will provide challenge to emergent findings and help synthesise and interpret the results. In addition, we will discuss project updates with people with diabetes through the NDA Experts by experience group. They will be invited to be part of integrative workshops to synthesise and interpret data from the three component studies.

## Study progress

We have gained ethical and Health Research Authority approval. In April 2025, we allocated 1283 primary care networks and emailed all intervention arm emails to via NHS England regions and integrated care boards to PCNs. We have begun delivery of the medium-intensity arm virtual workshops and started to send materials to the low-intensity arm sites.

## Discussion

The number of young adults with type 2 diabetes is increasing globally. There is evidence that they have poorer outcomes than other age groups with type 2 diabetes. Evidence-based care processes and improvement practices, such as case management and the promotion of self-management, can improve the achievement of blood glucose targets and reduce patient risk. There is variation between primary care networks in the achievement of blood glucose targets and the delivery of recommended care processes. Primary care networks receive feedback from the NDA describing the achievement of blood glucose targets and the delivery of recommended care processes. Providing feedback facilitation may increase the effectiveness of audit feedback. It is currently not clear how this might be delivered at scale to primary care networks across England. We will therefore test two interventions, deliverable at scale, that vary in intensity. Our pragmatic cluster randomized controlled trial with theory-informed process economic evaluation allocates all 1283 primary care networks in England to one of two interventions or waitlist control. Delivery to all primary care networks by the usual provider of similar interventions and using routine data demonstrates pragmatism, builds upon our previous embedded trial and takes a further step towards a national diabetes learning health system.

## Conclusion

Young adults with type 2 diabetes have a reduced life expectancy. Care and outcomes may be improved through the implementation of evidence-based practices. Evaluating the delivery of our specified interventions will provide valuable learning to intervention funders and deliverers. If effective, the interventions will improve both patient and service outcomes. If not effective, the evaluation will provide pragmatic lessons that inform future delivery and improve efficiency.

## Data Availability

Data sharing is not applicable to this article as no datasets were generated or analysed during the current study. The intervention manual is available from the corresponding author (MS).

## Appendix A

TIDieR framework [12] intervention description

**Table Taba:**

Item number		Low-intensity	Medium-intensity
1.	BRIEF NAME Provide the name or a phrase that describes the intervention.	The EQUIPD2 low-intensity feedback facilitation intervention	The EQUIPD2 medium-intensity feedback facilitation intervention
2.	WHY Describe any rationale, theory, or goal of the elements essential to the intervention.	See logic model	See logic model
3.	WHAT Materials: Describe any physical or informational materials used in the intervention, including those provided to participants or used in intervention delivery or in training of intervention providers.	e-Learning package supported by emails. The e-Learning package will be made available after the intervention period.	Powerpoint slides supported by emails. The slides will be made available after the intervention period.
		Both interventions contain further materials: Searches to identify patients, best practice guidance, checklists, recordings from young adults, videos from high-performing PCNs and links to publicly available web-resources.	
4.	WHAT Procedures: Describe each of the procedures, activities, and/or processes used in the intervention, including any enabling or support activities.	We will ask NHS regions to email PCNs, describing the intervention and providing a registration link. Registrants will be sent access to the e-Learning package or the virtual workshop invites.	
		e-Learning registrants will be able to opt-in to approximately 2-monthly emails intended to share learning and respond to both clinical and quality improvement questions. The responses will be general guidance not specific to patients or sites respectively.	Virtual workshop registrants will be sent diary invites for the virtual workshops. They will be given information about which virtual workshops are not recorded. They will select the dates for the didactic virtual workshops in advance. For the 5 interactive virtual workshops, they will receive invites for all virtual workshops and be asked to choose which they attend.
5.	WHO PROVIDED For each category of intervention provider (e.g. psychologist, nursing assistant), describe their expertise, background and any specific training given.	The intervention providers across both interventions are clinical experts, quality improvement leads. In addition, both interventions include asynchronous content provided by young adults with type 2 diabetes and clinical and non-clinical leads at high-performing PCNs.	
6.	HOW Describe the modes of delivery (e.g. face-to-face or by some other mechanism, such as internet or telephone) of the intervention and whether it was provided individually or in a group.	Via internet to the individual	Via MSTeams to multi-site groups. Each will have multiple date options. We will report on the size of these groups, which may vary based upon the dates participants choose to attend.
7.	WHERE Describe the type(s) of location(s) where the intervention occurred, including any necessary infrastructure or relevant features.	Internet	MSTeams
8.	WHEN and HOW MUCH Describe the number of times the intervention was delivered and over what period of time including the number of sessions, their schedule, and their duration, intensity or dose.	Sites will have access to 16 months. The eLearning takes approximately 90 mins to complete.	Sites will have access to 16 months. There will be 7 virtual workshops, two are more didactic, and 5 planned to be interactive.
9.	TAILORING If the intervention was planned to be personalised, titrated or adapted, then describe what, why, when, and how.	The interventions will not be tailored, but are intended to support local tailoring to identify influences and select actions that reflect local context.	

